# Mechanisms of neurodynamic treatments (MONET): a protocol for a mechanistic, randomised, single-blind controlled trial in patients with carpal tunnel syndrome

**DOI:** 10.1186/s12891-024-07713-6

**Published:** 2024-07-27

**Keywords:** Mechanisms, Neurodynamic, Carpal tunnel syndrome, Exercises, MRI, Quantitative sensory testing

## Abstract

**Background:**

Physiotherapeutic management is the first-line intervention for patients with entrapment neuropathies such as carpal tunnel syndrome (CTS). As part of physiotherapy, neurodynamic interventions are often used to treat people with peripheral nerve involvement, but their mechanisms of action are yet to be fully understood. The MONET (mechanisms of neurodynamic treatment) study aims to investigate the mechanisms of action of neurodynamic exercise intervention on nerve structure, and function.

**Methods:**

This mechanistic, randomised, single-blind, controlled trial will include 78 people with electrodiagnostically confirmed mild or moderate CTS and 30 healthy participants (*N* = 108). Patients will be randomly assigned into (1) a 6-week progressive home-based neurodynamic exercise intervention (*n* = 26), (2) a steroid injection (= 26), or (3) advice (*n* = 26) group. The primary outcome measure is fractional anisotropy of the median nerve at the wrist using advanced magnetic resonance neuroimaging. Secondary outcome measures include neuroimaging markers at the wrist, quantitative sensory testing, electrodiagnostics, and patient reported outcome measures. Exploratory outcomes include neuroimaging markers at the cervical spine, inflammatory and axonal integrity markers in serial blood samples and biopsies of median nerve innervated skin. We will evaluate outcome measures at baseline and at the end of the 6-week intervention period. We will repeat questionnaires at 6-months. Two-way repeated measures ANCOVAs, followed by posthoc testing will be performed to identify differences in outcome measures among groups and over time.

**Discussion:**

This study will advance our understanding of the mechanisms of action underpinning neurodynamic exercises, which will ultimately help clinicians to better target these treatments to those patients who may benefit from them. The inclusion of a positive control group (steroid injection) and a negative control group (advice) will strengthen the interpretation of our results.

**Trial registration:**

NCT05859412, 20/4/2023.

**Supplementary Information:**

The online version contains supplementary material available at 10.1186/s12891-024-07713-6.

## Background

Clinical guidelines recommend a conservative approach to entrapment neuropathies in people who present with mild to moderate symptoms [1–3]. Regardless of the type of entrapment neuropathy, the leading conservative treatments include steroid injection, and physical therapy [4, 5]. Various physical therapy modalities are offered as first-line interventions to manage symptoms before more invasive options (e.g., surgery) are considered [6–8]. Neurodynamic interventions have been incorporated as part of the physical therapy management of patients with peripheral nerve injuries, including entrapment neuropathies [8–10].

Neurodynamic interventions are aimed at restoring the homeostasis in and around the nervous system, by gliding the nerve in relation to its surrounding tissue while minimising neural strain [11–13]. These neurodynamic interventions facilitate the movement between neural structures and their surroundings (interface) by using a combination of joint movements or exercise [12]. Their efficacy has been confirmed as part of a combined intervention with education and splinting in some people with carpal tunnel syndrome (CTS) [14]. The uncertainty about the magnitude and specificity of these improvements in the wider population with CTS could be addressed by better understanding the mechanisms of action of neurodynamic exercises to identify those most likely to benefit.

Preclinical studies in animal models have investigated the mechanism of action of neurodynamic treatments suggesting an anti-inflammatory effect by reducing proinflammatory cytokines [15] and glial activation [16, 17]. There is also increasing in-vivo and in-vitro evidence that they may have a pro-regenerative and/or anti-degenerative effect on peripheral nerves [18–20] and can reduce the intraneural scar formation in a model of chronic constriction injury [21]. In humans, neurodynamic exercises in combination with other conservative treatments modified mechanical properties of peripheral nerves (i.e., decreased nerve stiffness) [22] and improved sensory and motor conduction velocities [23] along with pinch and grip strength [24]. Our previous study [25] showed changes in intraneural oedema using neurodynamic exercises only, but apart from T2 signal intensity, no advanced imaging or other mechanistic markers were included. How neurodynamic exercises in isolation can contribute to the pro-regenerative effect on peripheral nerves, changes in somatosensory function and the dispersion of inflammatory by-products are yet to be explored [25, 26].

A better understanding of how neurodynamic interventions work is an important first step towards personalised and precision physical therapy. We have previously shown that a set of eight nerve and tendon gliding exercises have a positive impact on symptoms [14] and can reduce MRI signals of oedema within the affected median nerve in patients with CTS [25]. CTS is an ideal model system to explore the mechanisms of action of neurodynamic treatments. It is the most common entrapment neuropathy [27] and provides good access to investigations of the function and structure of the affected nerve. We have demonstrated the presence of nerve degeneration and regeneration [26], intraneural [25], and systemic inflammation [28] using CTS as a model system. Importantly, patients with CTS are routinely treated with steroid injection (a potent anti-inflammatory medication), which has established short term benefits [29] and can therefore serve as a positive control treatment.

This single-blind randomised mechanistic controlled trial therefore uses CTS as a model system to investigate the mechanisms of action of a 6-week progressive home-based neurodynamic exercise intervention on nerve function, structure and neuroinflammation in patients with CTS compared to a positive control intervention (steroid injection) and a negative control intervention (advice). We will also include a healthy control group who will provide normative data on nerve structure, function, and inflammatory markers. The deep and comprehensive phenotyping of our patient cohort includes different advanced neuroimaging sequences (i.e., diffusion, T2 mapping and anatomical images with magnetisation transfer preparation) that combined with our functional (i.e., quantitative sensory testing, nerve conduction studies, serum protein levels in blood) could help disentangle the mechanisms of action of neurodynamic exercises locally. In future analyses, we will explore whether these neurodynamic exercises have an effect proximally at the level of the dorsal root ganglia (DRG).

## Methods

This randomised, mechanistic, single blind, controlled trial will be carried out at Oxford University, UK, and will be reported according to the CONSORT guidelines [30].

### Participants

We will include people with a confirmed diagnosis of mild or moderate of CTS based on clinical [31] and electrodiagnostic [32] criteria.

We will identify eligible patients from the neurophysiology department at Oxford University Hospitals Foundation NHS Trust (OUH), primary care services and through public advertisement (flyers, leaflets, community notice boards, emailing lists and social media). An age and gender matched cohort of healthy volunteers recruited through flyers, leaflets, community notice boards, emailing lists and social media will be included to establish normative data.

Inclusion criteria for people with CTS and healthy controls include being 18 years or older, willing, and able to give informed consent for participation in the study, and having sufficient command of the English language to complete questionnaires and the detailed assessments. The electrodiagnostic testing will include median, ulnar and radial nerve sensory and motor studies to determine the presence of CTS and the absence of other peripheral neuropathies, according to established protocols [32]. The temperature of the hand will be standardised before testing to > 31 °C. Sensory nerve action potential latencies, amplitudes and nerve conduction velocities will be recorded orthodromically over the wrist for the median (index finger), ulnar (little finger) and superficial radial nerve (snuffbox). Compound muscle action potentials will be registered for the median nerve (abductor pollicis brevis stimulated from the wrist and antecubital fossa), and ulnar nerve (adductor digiti minimi stimulated from the wrist, below and above the elbow). Additionally, we will record orthodromic sensory nerve action potentials by stimulating the ring finger and register the response at the wrist. The presence of a ‘double peak’ (increased latency of median sensory nerve action potential compared to ulnar sensory nerve action potential) will be classified as abnormal [33]. The motor latency difference between the median nerve (second lumbrical) and ulnar nerve (palmar interossei) will be assessed over a fixed distance of 8 cm with a delay of the median motor potential relative to the ulnar latency > 0.4 ms deemed abnormal [34].

The severity of CTS will be graded according to Bland’s criteria [32]. Only patients with mild (sensory conduction velocity from index finger to wrist < 40 m/s with motor terminal latency from wrist to abductor pollicis brevis [APB] < 4.5 ms) and moderate CTS (motor terminal latency > 4.5ms and < 6.5ms with preserved index finger sensory nerve action potential) will be included. People with severe CTS are recommended surgery according to clinical guidelines [1, 2] and thus will not be included in this study.

People with CTS will be excluded if they had previous ipsilateral CTS surgery (patients with unilateral surgery on the non-study hand are eligible to participate) or are planning to undergo surgery in the next 6 weeks, had a steroid injection for their CTS in the 6 months prior to the study enrolment or who had already more than 1 steroid injection, have an electrodiagnostic test that reveals abnormalities other than CTS (e.g., ulnar neuropathy), present with another medical condition affecting the upper limb or neck (e.g., rheumatoid arthritis, cervical radiculopathy or myelopathy), a history of significant trauma to the upper limb or neck, diabetes, hypothyroidism, severe anxiety or depression, altered coagulation (e.g., haemophilia) or having strong anticoagulant medication that prevents skin biopsies, contraindications for steroid injections (e.g., infection of the skin, allergy to any components of the injection) or for MRI (e.g., metallic implants), or those who are pregnant, lactating or planning pregnancy during the course of the study. Healthy participants will be excluded if they present with a history of hand, arm or neck pain in the past three months, abnormalities in nerve conduction studies suggestive of CTS, or with a systemic medical condition.

### Study procedure

Consented participants (see ethics below) will receive the baseline set of questionnaires to complete before the first baseline appointment at the Nuffield Department of Clinical Neurosciences, University of Oxford. This first appointment will include a detailed bedside neurological assessment and measures of nerve function. If participants present with bilateral symptoms of CTS, the most affected hand will be evaluated. At this point, participants not meeting the inclusion criteria will be excluded from the study (e.g., severe electrodiagnostic test findings). Eligible participants will provide a blood sample and a finger skin biopsy.

Participants will be invited for a second baseline appointment for an MRI of the wrist and the neck. Following the scan, patients will receive their assigned intervention. After the 6-week intervention period, patients will be invited for a follow-up appointment to repeat the same assessments. Finally, questionnaires will be sent out to patients at 6 months (Fig. 1).

Healthy controls will only attend the baseline appointments during which the same measures will be performed as in patients.

**Fig. 1 Fig1:**
[figure not shown]
Trial flow chart

### Assignment of interventions and blinding

Patients will be randomly assigned to one of three interventions after their first baseline appointment. Assignment will be randomised and stratified by electrodiagnostic test severity (mild/moderate) using an online tool (https://www.randomizer.org) and implemented in REDcap. The allocation ratio will be 1:1:1. The examiner performing the outcome measures will be blinded. The central research team, including the statistician, will also be blinded.

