### Safety and adherence to neurodynamic exercises

Patients assigned to the neurodynamic exercise group will be asked to complete an electronic (or paper-based) exercise diary daily to monitor treatment adherence for the duration of the intervention (6-weeks). Patients will be asked to indicate how many times they perform the exercises each day.

We will also use periodic phone calls during the 6-week study period (3rd day after randomisation, weekly thereafter) to check on progress in each of the intervention groups, decrease study attrition, give advice on exercise performance when needed, check if there are potential adverse events associated with the exercise intervention or the steroid injection, and to confirm that they have not started any new treatments during the intervention period in the steroid and advice groups. This was suggested by our patients’ partners to increase adherence.

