### Statistical analysis

Data will be analysed using R Studio (v 7.2, RStudio, Boston, USA) [58]. The distribution of the data will be checked for normality, and parametric, or non-parametric methods will be used as appropriate. Participants’ characteristics in each group will be described at baseline.

Two-way repeated measures ANCOVAs (factors time and intervention, adjusted for baseline measurements as a continuous covariate) followed by post-hoc testing will be performed to identify differences in primary/secondary outcome measures among groups and over time. If there is deviation from normality, we will use non-parametric alternatives (i.e. ranked ANCOVA).

If the missing values mechanism is likely to be missing at random (MAR) or missing completely at random (MCAR), we will perform multiple imputation by chained equations. The appropriate model will be fitted in all the completed datasets, then coefficient estimates and standard errors will be pooled across imputations using Rubin’s rules.

The level of statistical significance will be set at *p* = 0.05. Adjustments for multiple comparisons will be used as appropriate.

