### Patient and public involvement (PPI)

Patient partners highlighted the relevance of this study. They were involved in the design of the videos in the neurodynamic exercise group (i.e., including demonstrative videos with either right or left hand) and how these videos should be displayed (i.e., individual videos explaining each exercise and a summary video with the full sequence). Additionally, they provided feedback on the potential burden of the duration of the baseline assessment and suggested two separate appointments (i.e., MRI on a separate day). They agreed on the feasibility to perform the sessions suggested in the home-based neurodynamic intervention. They suggested ways to optimise the adherence to the neurodynamic intervention by facilitating access to the home-based program using different devices (i.e., computer or mobile phones), and the use of electronic and paper-based exercise diaries along with daily email reminders to input the number of exercise sessions per day.

Patient partners will continue to be involved throughout the study (e.g., suggestions with recruitment, sense-making, interpretation of the data, evaluation of the output) and to help with the dissemination of the findings. The dissemination of our findings will involve publication in scientific journals, social media outlets, webinars, electronic newsletters, presentations at conferences, as guided by our patient partners. We will adapt the content of our findings to health care professionals, researchers and people with CTS according to our PPIs suggestions.

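### Randomisation appears to precede the baseline wrist MRI, so a patient lost between the two is already randomised without a baseline for the primary outcome, and the phone calls are dated from the wrong event

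*Protocol article*

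**What the plan says.** The order of events has to be pieced together from several sections of the protocol article.

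- **Assignment of interventions and blinding:** "Patients will be randomly assigned to one of three interventions after their first baseline appointment". Allocation is 1:1:1, stratified by electrodiagnostic severity and implemented in REDCap. On blinding: "The examiner performing the outcome measures will be blinded".
- **Study procedure:** the first appointment covers the neurological assessment, nerve function, blood and skin biopsy. Then: "Participants will be invited for a second baseline appointment for an MRI of the wrist and the neck". Then: "Following the scan, patients will receive their assigned intervention".
- **Patient and public involvement:** patient partners "suggested two separate appointments (i.e., MRI on a separate day". The length of the gap is not given.
- **Abstract, Methods:** "The primary outcome measure is fractional anisotropy of the median nerve at the wrist using advanced magnetic resonance neuroimaging".
- **Statistical analysis:** the ANCOVAs are "adjusted for baseline measurements as a continuous covariate". Multiple imputation is planned if data are missing at random or completely at random.
- **Safety and adherence to neurodynamic exercises:** there will be "periodic phone calls during the 6-week study period (3rd day after randomisation, weekly thereafter". The calls check progress in every group, support exercise performance, limit attrition and ask about adverse events of the exercises or the injection.
- **Sample size calculation:** 63 patients are needed, and 78 are included to allow for 20% drop-out.

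**The concern.** In a trial whose primary endpoint is adjusted for its own baseline, that baseline is best secured before the patient is committed to an arm. Here the first-appointment measures precede allocation. Only the MRI measures, which include the primary outcome, appear to follow it.

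The exposure is to loss in the gap. A patient who drops out before the scan belongs to the randomised population but contributes neither a baseline nor, in all likelihood, a follow-up value of FA. If the patient already knows the arm, leaving may be related to it, for example through reluctance about an injection or disappointment at receiving advice only. Imputation under a missing-at-random assumption would then be harder to defend. Randomising after the scan prevents this kind of loss altogether.

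The call schedule raises a second, smaller matter. It treats randomisation as if it were the start of treatment, which the other two sections do not ensure.

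**Working it through.** **1. Sequence.** Setting the sections side by side gives: first appointment → randomisation → (separate day, interval not stated) → baseline wrist MRI → intervention. Randomisation is tied to the first of two named baseline appointments, and what the patient receives after the scan is described as already assigned. Reading the randomisation sentence as meaning after both appointments is possible but strained. If that was intended, the text still needs correcting.

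**2. Call schedule.** Let g be the number of days from randomisation to the MRI visit, which is also the start of treatment. Assume weekly calls counted on from day 3, so days 3, 10, 17 and so on after randomisation. The first call falls on treatment day 3 − g.

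| g (assumed) | First call relative to treatment start | Calls before treatment |
|---|---|---|
| 2 days | day +1 | 0 |
| 7 days | day −4 | 1 (day 3) |
| 14 days | day −11 | 2 (days 3 and 10) |

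The schedule fits a progress and adverse-event check only if g is at most about three days, and no section fixes that.

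**3. The plan's own sample size.** 63 / 0.8 = 78.75, so 79 exactly, against 78 stated. In reverse, 78 × 0.8 = 62.4 against 63 required. The figure reproduces to within one patient. The plan can lose 78 − 63 = 15 patients (15/78 = 19.2%) before it falls below its target, and each patient lost before the scan uses one of those 15.

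**4. How likely is any such loss?** The article gives no rate. With an assumed independent per-patient probability p, the chance of at least one case in 78 is 1 − (1 − p)^78:

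- p = 1%: 54%
- p = 2%: 79%
- p = 5%: 98%

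**5. Outer bound on the effect.** Suppose a share x has no baseline scan *in addition to* the full 20% drop-out. Complete pairs are then 78 × (1 − x) × 0.8. For power I read the stated 0.22 (labelled d) as Cohen's f and take the group-by-time interaction with 3 groups and 2 time points: noncentrality f²·N·2/(1 − ρ), degrees of freedom 2 and N − 3, with N rounded down. The correlation ρ is not stated. The 63 is reproduced at 80% power only for ρ of about 0.40 to 0.42 (power at 63: 0.801 to 0.815); ρ = 0.5 would need only 54.

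| x (assumed) | Complete pairs | Power, ρ = 0.42 | Power, ρ = 0.5 |
|---|---|---|---|
| 0% | 62.4 | 0.808 | 0.866 |
| 2% | 61.2 | 0.801 | 0.860 |
| 5% | 59.3 | 0.786 | 0.846 |
| 10% | 56.2 | 0.762 | 0.825 |

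If the 20% already includes pre-scan losses, the first row applies and nothing changes.

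**The case against.** The case against is substantial, and most of it stands.

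- *The baseline is not contaminated.* The scan precedes treatment and the outcome examiner is blinded. A reader might infer that a covariate measured after randomisation biases the ANCOVA. The article gives no mechanism for that, and I do not claim it.
- *No missing scans are documented.* A reader might conclude that some randomised patients will certainly lack a baseline scan. The article neither says so nor gives a rate, and it excludes patients with MRI contraindications. Step 4 shows that at least one case is likely at modest assumed rates, but those rates are assumptions.
- *Patients may not know their arm before the scan.* The exercise leaflet is handed over at the second appointment, which suggests that disclosure may come then. Loss related to arm, or a phone call that reveals the arm before the scan, is therefore only a possibility. The full protocol or the flow chart, neither of which is shown, may settle it.
- *Power loss is not demonstrated.* Withdrawal before the scan is ordinary drop-out and may well sit inside the 20%. The falls in step 5 stack losses and depend on an unstated correlation.
- *Imputation is planned.* It can also help where only the baseline scan is unusable, since a 6-week scan may still exist. It recovers little FA information for a patient who leaves before any scan.
- *The call wording may mean the gap is short.* Placing day 3 after randomisation inside the 6-week period suggests that randomisation and treatment were expected to nearly coincide. That narrows the concern, but nothing in the procedure secures it.

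What remains is the ordering itself, the unstated interval and time of disclosure, and the mismatch in the call schedule.

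**Conclusion.** The point holds as a cheap improvement, of minor to moderate severity and with medium confidence. As written, randomisation most naturally comes before the baseline measurement of the primary outcome, on a different day, with no stated interval. This opens an avoidable window for post-randomisation loss of baseline FA, possibly related to arm.

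The size is unknown. It may be nil if the 20% allowance absorbs these losses, but that allowance has nothing to spare. At an assumed extra 10%, power would be about 0.76 (ρ = 0.42) to 0.83 (ρ = 0.5), which is an outer illustration and not a forecast. The ordering and call-schedule points do not depend on any of the power figures. The sections on study procedure, assignment of interventions, and safety and adherence must be reconciled.

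**What to change.** Release the REDCap allocation at the second baseline appointment, after the wrist MRI has been acquired and checked as usable and immediately before the intervention. State this once and align the other sections with it. Date the phone calls from the start of the intervention instead of from randomisation.

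If the present order has to stay, state the interval between the appointments, when allocation is disclosed to the patient, and how randomised patients without a usable baseline scan are analysed.

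The cost is a procedural amendment. No visit or staff need be added, because treatment already follows the scan and allocation already runs in REDCap. The scan needs a quick usability check on the day, and the injecting doctor's slot must be held or booked before the arm is known.
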